### Statistical analysis

#### Sample size

To study the non-inferiority of the 50% reduced betamethasone dose regimen, we will test the alternative hypothesis that the difference in failure rate between the half-dose and the full-dose arm do not exceed 4% (corresponding to a Relative Risk of 1.20). This non-inferiority margin has been obtained through a consensus between the investigators of the GROG, neonatologists and the methodologists of the study, considering that a 4% difference is the smallest value that would be clinically relevant between arms and correspond to the preservation of a 70% of the effects of the full dose betamethasone regimen over placebo. Indeed, in the French Epipage2 study (2011) [51], 62% of the neonates exposed to antenatal betamethasone and born before 32 weeks of gestation from a singleton pregnancy received exogenous surfactant. Assuming that 33% (conservative hypothesis) of the randomised women will indeed deliver before 32 weeks, we estimated that 20% of the included pregnant women receiving the full betamethasone dose regimen would have a neonate with severe RDS, defined as the need for exogenous intra-tracheal surfactant. According to the literature, ACS is responsible for an average relative risk of RDS of 0.66 (95% CI 0.56 to 0.77), compared to placebo [8, 52]. Assuming a prevalence of severe RDS of 20% in the full dose betamethasone regimen, to preserve 67% of the upper bound for the historical difference between full dose and placebo (i.e. 0.67 x (0.20–0.20/0.77)) gave a margin of 4% (or expressed as Relative Risk (20 + 4) / 20 = 1.20). Thus, 1571 patients in each treatment group are required to test the non-inferiority hypothesis, with a 1-sided type-1 error of 0.025, a power of 0.80, and a non-inferiority margin equal to 4% [53].

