#### Interim analysis

To address the ethical concerns of (i) studying a high-risk population (pregnant women and preterm neonates), (ii) the potential increased rates of babies with severe RDS due to the reduction of the betamethasone dose, (iii) the anticipated length of time of inclusion (30 months), (iv) the number of infants planned for a fixed analysis (*n* = 3142) and (v) the primary endpoint measured in the first 48 h of life, a sequential data analysis method will be used, allowing to provide stopping rules. Analyses will be done after every 300 neonates who reach the primary outcome on the basis of intention to treat. The trial may be stopped for the following reasons:i.Inferiority of the experimental group on the primary outcome,ii.Non-inferiority of the experimental group on the primary outcome,

Finally, a maximum of 11 analyses is planned.

For the primary outcome, a non-inferiority sequential design with alpha and beta spending functions will be used to control the first type and second type error, respectively. For the estimation of the boundary curves, we chose a monotone function proposed by *Kim and DeMets* and generalized by *Jennison and Turnbull* [55, 56]. Critical values of the boundary curves are defined for each interim analysis. At each interim analysis, the maximum likelihood estimator of the difference of treatment failure rates between full-dose and half-dose will be compared to these critical values and the necessity to stop the trial will be checked.

In addition to that sequential primary analysis, the rate and percentage of the four safety outcomes (marked above with an *: neonatal death, IVH grade 3 and 4, NEC grade ≥ 2, and retinopathy of prematurity treated by anti-VEGF or laser) will be estimated in order to detect a potential increasing in the experimental group. Those estimation will be made on the overall population, and by gestational age at birth (born before 28 weeks, between 28 and 32 weeks, and after 32 weeks), as expected prevalence are different from one subgroup to the other.

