### Safety monitoring

The trial safety will be evaluated by an independent Data Safety Monitoring Board (DSMB) at each interim analysis or when additional analyses will be requested by the sponsor or the steering committee. The DSMB will include experts in or representatives of the fields of obstetrics, neonatology, and clinical trials methodology. At the first time they met, the DSMB will validate that the methodology is compatible with the safety of the participants. Prior to each DSMB meeting, they will be provided a complete list of all adverse events, and a statistical report including description of the population and results of the interim analysis as described above. At each meeting, the DSMB may give the advice to temporarily or definitely stop the trial if in their opinion there is an unexpected or unacceptable risk for the women or the newborn, or if the interim analysis suggests the non-inferiority or futility.

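### Stopping reason (i) is called inferiority, but the only boundary described for it is a beta-spending (futility) boundary, and Safety monitoring calls the interim stop futility

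*Protocol article*

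**What the plan says.** The Interim analysis section gives two reasons for stopping. The first is "Inferiority of the experimental group on the primary outcome" and the second is non-inferiority. For the method it says that "alpha and beta spending functions will be used to control the first type and second type error, respectively". It gives no separate test for inferiority and no error level for one.

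The Safety monitoring section lets the data safety monitoring board (DSMB) advise stopping "if the interim analysis suggests the non-inferiority or futility". Inferiority is not mentioned there.

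The Sample size section supplies the error rates: a one-sided type I error of 0.025, "a power of 0.80" and a margin of 4 percentage points. It concludes that "1571 patients in each treatment group are required to test the non-inferiority hypothesis".

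**The concern.** Futility and inferiority are different conclusions. Alpha spending controls the risk of wrongly claiming non-inferiority. Beta spending controls the risk of failing to claim it when it is true. Crossing a beta-spending boundary says that non-inferiority is unlikely to be shown. It is not set up as a test that half dose is worse than full dose.

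With the label inferiority on that boundary, an early stop could be described as evidence against the half dose when the data are compatible with no difference. The article also gives two descriptions of what appears to be one stop.

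**Working it through.** **Inputs.** From Sample size: full-dose failure rate 20%, margin 4 points, one-sided alpha 0.025, beta 0.20, 1571 per arm (3142 in total). From Interim analysis: a look every 300 neonates, at most 11 analyses, a Kim-DeMets type spending function.

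**Assumptions.**
- The spending function is the power family, error × t^rho, with t the information fraction. Rho is not stated, so 2 to 3 is taken as the main range and 1 as a wider check.
- The last look is at 3142, or at 11 × 300 = 3300.
- The true rates are equal at 20%.
- The 300 neonates per look are neonates assessed, not events, because only about 0.20 × 3142 = 628 events are expected.

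**1. The plan's own figure.** n per arm = (1.960 + 0.842)² × 2 × 0.20 × 0.80 / 0.04² = 7.849 × 0.32 / 0.0016 = 1,569.8, so 1570 against the stated 1571. It is reproduced with a true difference of 0. The plan's type II error is thus the chance of not showing non-inferiority when the arms are identical.

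**2. Chance of crossing at an interim look, identical arms.** With total beta 0.20, the amount spent by the tenth look (3,000 neonates) is 0.20 × t^rho.

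| rho | last look 3142: t = 3000/3142 = 0.955 | last look 3300: t = 3000/3300 = 0.909 |
|---|---|---|
| 1 | 19.1% | 18.2% |
| 2 | 18.2% | 16.5% |
| 3 | 17.4% | 15.0% |

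A numerical recursion over the looks to 3142 gives 17.8% (rho 2) and 16.9% (rho 3).

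If instead the two boundaries are forced to meet at 3142, total beta must rise to 0.248 (rho 2) or 0.226 (rho 3). The interim part is then 0.248 × 0.955² = 22.6% or 0.226 × 0.955³ = 19.7%.

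**3. What a crossing shows.** This is the observed difference (half minus full dose, percentage points) at the boundary with total beta 0.20 and last look 3142. The nominal 95% interval uses SE = √(0.32 / n per arm); at 1,800 neonates, √(0.32/900) = 1.89 points.

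| Neonates | rho 2 | rho 3 |
|---|---|---|
| 1,200 | 4.7 (0.2 to 9.2) | 5.5 (1.0 to 10.0) |
| 1,500 | 3.8 (−0.2 to 7.9) | 4.4 (0.3 to 8.4) |
| 1,800 | 3.2 (−0.5 to 6.9) | 3.6 (−0.1 to 7.2) |
| 2,400 | 2.2 (−1.0 to 5.4) | 2.4 (−0.8 to 5.6) |
| 3,000 | 1.6 (−1.3 to 4.4) | 1.5 (−1.4 to 4.4) |

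With the boundaries forced to meet and rho = 3, the values are 3.4 (−0.3 to 7.1) at 1,800, 2.2 (−1.0 to 5.4) at 2,400 and 1.3 (−1.5 to 4.2) at 3,000. The pattern is the same. These intervals are not adjusted for repeated looks.

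**4. Where the crossings fall.** At rho = 3 the nominal interval at the boundary excludes zero up to 1,500 neonates. By then 0.20 × (1500/3142)³ = 2.2 of the 17.4 percentage points have been spent, so 15.2 fall at 1,800 or later. At rho = 2 it excludes zero up to 1,200 neonates. By then 0.20 × (1200/3142)² = 2.9 of 18.2 points have been spent, which leaves 15.3 for later looks.

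**The case against.** The strongest reply is that this is one loose word and that the rest of the article limits its effect. Final analyses reports the difference with its confidence interval against the margin and plans only to claim non-inferiority or not. Safety monitoring already says futility. Stopping is discretionary in both sections. This stands, and it lowers the stakes: a reader might infer that a futility stop will be published as inferiority, but no such claim is planned anywhere in the article.

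A second reply is that inferiority may be shorthand for accepting the null hypothesis that half dose is worse by at least 4 points. That reading is possible, but it does not rescue the label. At the mid to late looks the estimate at the boundary is below 4 points, so a crossing there does not establish an excess of that size either.

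A reader might also infer that about one trial in five with identical arms would be stopped as inferior. The documents do not support that as a fact. The full 0.20 is reached only by counting failures at the final analysis. Interim figures of 20% to 23% need a total beta above the stated 0.20. All these figures are crossing probabilities, not certain stops.

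Nor does every crossing show no more than futility: at early looks it takes a large observed excess, and the nominal interval can exclude zero.

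**Conclusion.** The point holds as a contradiction of labels in an operative stopping rule. The Interim analysis section names inferiority for a stop whose only described basis is beta spending, and Safety monitoring names futility.

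With identical arms, the chance of crossing at an interim look is roughly 15% to 18% (beta 0.20, rho 2 to 3), or about 20% to 23% if the boundaries are forced to meet at 3142. For scale, a one-sided test against zero at 2.5%, a level assumed here and not in the plan, would call at most 1 in 40 such trials inferior. Most crossings fall at looks where the interval at the boundary includes zero.

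The sizes rest on the unstated rho, the reading of the look schedule and equal true rates of 20%; the contradiction itself does not. The boundary is not shown to be wrong. Because the final report would show the interval, the likely harm is moderate, but the correction is worth making.

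**What to change.** In Interim analysis, replace reason (i) with *futility: non-inferiority is unlikely to be shown*, and use the same term in Safety monitoring. Add one sentence: crossing this boundary leads to the conclusion that non-inferiority was not shown, and *inferior* is used only if a sequentially adjusted confidence interval for half minus full dose lies wholly above 0.

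The cost is wording in the protocol, and in the analysis plan and DSMB charter if they carry the same label. No patients are added, and the boundaries and sample size stay as they are.

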#### Final analyses

Data analysis and reporting will follow the CONSORT guidelines for non-inferiority randomised controlled trials [57]. The two groups will be compared for women’s and neonate’s characteristics. Qualitative variables will be summarised by numbers and percentages of patients in each treatment group.

The final primary non-inferiority statistical analysis will be conducted on all the neonates enrolled in the trial, including those who did not participate in the interim analysis. The difference between the failure rates observed in both arms along with its 2-sided confidence interval will be estimated. The final boundary for difference will be compared to the critical value corresponding to the number of women finally included, to claim or not the non-inferiority. A figure showing confidence intervals and the margin of non-inferiority will be used to summarize the result on the primary outcome.

The analyses on the other pre-specified secondary outcomes will consist in estimations and comparisons between the two arms. The 95% confidence interval for the difference between arms will be constructed. The χ2 or Fisher’s exact test for categorical variables and Student or Mann-Whitney-Wilcoxon test for continuous variables will be used to compare the full-dose and the half-dose regimens, according to the validity conditions. All these statistical tests will be two-sided and the level of statistical significance will be set at 5% (2-sided).

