### Setting

Thirty-seven French level 3 maternity units will be involved (Additional file 1).

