#### Allocation of treatment and blinding

After obtaining maternal consent, randomisation is performed just before the second injection, using a web-based application and a secured access, in a one-to-one ratio to the full or half dose groups according to a computer-generated list of randomly permuted blocks. The randomisation is stratified by maternity units and gestational age (before or after 28 weeks). The randomisation list is centrally computer-generated and a web-based application ensures proper allocation concealment. The allocation sequence is not available to any member of the research team until the database will be completed and locked. Patients, care providers and outcome assessors are masked to assignment. A study number is allocated to the woman corresponding to a treatment pack, each of which looks identical and contains two opaque study-labeled vials.

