#### Secondary outcome measures

The secondary assessment criteria will be measured during the neonatal period until hospital discharge for children born at term and not later than 37 weeks of PMA for the premature babies. They will include:Respiratory distress syndrome defined within the first 72 h as the use of continuous positive airway pressure and/or supplemental oxygen during at least 24 h, or the use of mechanical ventilation.Transient tachypnea of the newborn defined as a need for continuous positive airway pressure and/or supplemental oxygen, resolving within 24 h.Outcomes related to the severity of RDS:○ Highest appropriate fractional inspired oxygen (FiO2),○ Maximum appropriate Mean Airway Pressure (MAP),○ Use and duration of mechanical ventilation,○ Use and duration of oxygen therapy,○ Need for oxygen therapy after 36 weeks post conception.Outcomes related to betamethasone impact on other prematurity-induced complications:○ Neonatal death before discharge*,○ Admission to neonatal intensive care unit,○ Use of inotropic support including dopamine, epinephrine, dobutamine, and norepinephrine,○ Pneumothorax,○ Patent ductus arteriosus requiring either medical or surgical treatment,○ Bronchopulmonary dysplasia at 36 weeks of PMA (need for continuous positive airway pressure or supplemental oxygen, or mechanical ventilation),○ NEC and grade according to Bell classification [49],*○ IVH and grade according to the Papile classification [50],*○ Cystic periventricular leukomalacia,○ Use of postnatal steroids (either inhaled or systemic),○ Retinopathy of prematurity requiring anti-VEGF treatment or laser*,○ Length of hospital stay before the first discharge home,○ Survival without severe RDS, IVH grade 3 and 4, NEC grade ≥ 2, or retinopathy of prematurity treated by anti-VEGF or laser.Outcomes related to potential adverse events of betamethasone○ Birth weight at birth,○ Head circumference at birth,○ Body length at birth,○ Suspected or confirmed early onset sepsis treated using antibiotics during 7 days,○ Hypoglycaemia requiring oral or IV glucose administration or glucagon within 7 days.

Outcomes marked with an asterisk * are the four *safety outcomes* that will be monitored at each interim analysis.

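### Randomisation is stratified by maternity unit and gestational age, but the analyses described ignore the strata; the crude interval is valid, yet wider than needed if the strata are prognostic

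*Protocol article*

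**What the plan says.** On allocation, the protocol article (Allocation of treatment and blinding) states: "The randomisation is stratified by maternity units and gestational age (before or after 28 weeks". Women are assigned "in a one-to-one ratio to the full or half dose groups according to a computer-generated list of randomly permuted blocks". Under Setting, "Thirty-seven French level 3 maternity units will be involved", so there are 37 x 2 = 74 randomisation strata.

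On the primary outcome, Final analyses says "The difference between the failure rates observed in both arms along with its 2-sided confidence interval will be estimated". Interim analysis says "the maximum likelihood estimator of the difference of treatment failure rates between full-dose and half-dose will be compared to these critical values". Neither sentence mentions centre or gestational age, and the method for the confidence interval is not named.

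On secondary outcomes, Final analyses names chi-square or Fisher's exact tests for categorical variables, and says "Student or Mann-Whitney-Wilcoxon test for continuous variables will be used to compare the full-dose and the half-dose regimens". The continuous outcomes include "Birth weight at birth", head circumference and body length.

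Subgroup analyses uses gestational age at birth and sex of the newborn. Those are not the randomisation strata, and they do not yield a stratified overall estimate.

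**The concern.** Balanced allocation within prognostic strata lowers the true sampling variance of the difference between arms. The usual two-sample standard error does not reflect this. It still contains the between-stratum variation that the design has removed, so the interval is too wide. In a non-inferiority trial the interval limit is compared directly with the margin, so an over-wide interval lowers the chance of showing non-inferiority when it is true. What is at stake is efficiency: some precision that stratified randomisation makes available is not used. The same applies to the unstratified secondary tests.

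**Working it through.** **Inputs from the article.** Full-dose failure rate 20% (Sample size: "Assuming a prevalence of severe RDS of 20% in the full dose betamethasone regimen"), true difference 0, margin 4 points, one-sided error 0.025, power 0.80, 1571 per arm, 37 centres, two gestational-age strata, 1:1 permuted blocks.

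**Inputs assumed, because the article gives no failure rate by stratum or centre.** Share randomised before 28 weeks w = 35% (20-50% also tried); difference in failure rate between the two gestational-age strata d = 0 to 30 points with the overall rate held at 20%; between-centre SD 0 or 5 points; blocks of 4 in the simulation.

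**1. Reproduce the stated size.** n = 2 x 0.20 x 0.80 x (1.96 + 0.84)² / 0.04² = 1569.8 with unrounded normal quantiles, so 1570 per arm; the Farrington-Manning form gives 1573. The stated 1571 is reproduced as an unstratified, fixed-design figure. At 1571 per arm the crude standard error is sqrt(0.32/1571) = 0.01427, the 95% half-width is 1.96 x 0.01427 = 2.80 points, and power is 80.0%.

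**2. Variance removed by stratification.** R = [w(1-w)d² + SD²] / [p(1-p)], with p(1-p) = 0.16. For example, w = 0.35, d = 0.20 and SD = 0.05 give (0.0091 + 0.0025)/0.16 = 7.3%. Power is then Phi(0.04/(0.01427 x sqrt(1-R)) - 1.96).

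| d (rates before / after 28 weeks) | R, age and centre | Power by formula | Half-width, points | Equivalent n per arm | R, age alone | Power, age alone |
|---|---|---|---|---|---|---|
| 10 points (26.5% / 16.5%) | 3.0% | 81.2% | 2.76 | 1524 | 1.4% | 80.6% |
| 20 points (33.0% / 13.0%) | 7.3% | 82.9% | 2.69 | 1457 | 5.7% | 82.3% |
| 30 points (39.5% / 9.5%) | 14.4% | 85.7% | 2.59 | 1345 | 12.8% | 85.1% |

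If neither factor is prognostic, R = 0 and power stays at 80.0%. Centre alone with SD 5 points gives 0.0025/0.16 = 1.6%. The most favourable case tried (w = 50%, d = 30 points, SD 5 points) gives R = 15.6% and 86.2%.

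**3. Simulation.** 37 centres x 2 strata, N = 3142, w = 35%, 8000 runs per scenario; crude Wald interval against the Mantel-Haenszel risk difference with Sato variance. Centre SD is 5 points in the prognostic scenarios and 0 in the first row.

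| d | Power crude | Power stratified | Gain, points | One-sided error at the margin, crude / stratified |
|---|---|---|---|---|
| 0 | 80.5% | 80.6% | 0.1 | - |
| 10 points | 80.7% | 81.6% | 0.9 | 0.024 / 0.026 |
| 20 points | 81.5% | 83.2% | 1.7 | 0.020 / 0.023 |
| 30 points | 81.2% | 85.2% | 4.0 | 0.017 / 0.024 |

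The simulated gain is smaller than the formula's gain over 80.0%, because stratified allocation already lifts the crude analysis slightly. At d = 20 points the two estimates have almost the same true SD (0.01378 crude, 0.01379 stratified), while the crude analysis reports a standard error of 0.01426. The gain therefore comes from the standard error, not from a better point estimate.

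**4. Strata at the first look.** 300/74 is about four neonates per centre-by-age cell. By gestational age alone, with w = 35%, the strata hold 300 x 0.35 = 105 and 300 x 0.65 = 195.

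**The case against.** Four arguments on the other side have force.

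- **The design never relied on the unused precision.** The 1571 is a crude calculation, and the crude analysis reached at least 80% in every simulated scenario. Its error is on the safe side. This stands: the point is about efficiency, not validity.
- **The prognostic strength is not documented.** Interim analysis says only that the prevalence of the safety outcomes differs by gestational age at birth. The Sample size section ties severe RDS to birth before 32 weeks (0.62 x 0.33 = 20.5%), which again concerns age at birth. If the 62% surfactant rate held in both strata, d = 30 points would need 39.5/62 = 64% of women to deliver before 32 weeks in one stratum against 9.5/62 = 15% in the other. Nothing in the article supports or excludes that. This stands: the size is a range that starts at zero.
- **The analysis plan is not shown.** The Ethics section says that one exists, and the interval method is often left to it. This stands in part. The unstratified variance for the primary interval is inferred from the crude estimator that the article names. The unstratified secondary tests are stated outright.
- **Full stratification is awkward at early looks.** With about four neonates per cell, this stands, and it limits the role of centre.

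A reader might also infer that the sequential design already falls short of 80% and needs this precision back. The article does not give the spending parameters, so that cannot be established from it. A reader might further conclude that birth weight, length and head circumference should be analysed only as gestational-age-specific scores. Such scores condition on gestational age at birth, which arises after randomisation, and so answer a different question. The raw comparison is unbiased. Any precision gain from the scores depends on a growth curve and a distribution of birth timing that the article does not give.

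**Conclusion.** The concern holds as a recommended improvement of modest size. The article stratifies the randomisation and then describes a crude primary difference and unstratified secondary tests. With stratum differences of 10 to 30 points, 35% of women randomised before 28 weeks and a between-centre SD of 5 points, stratified analysis removes about 3-14% of the variance and adds about 1-4 points of power. Gestational age alone accounts for most of this (about 1-13% of the variance by formula). If the strata do not predict surfactant use, the gain is nil. The crude interval is valid and conservative, so this source carries no risk of a false non-inferiority claim, and the fixed-design 80% does not depend on the change. It would be too strong to say that the planned analysis is invalid, that the trial is underpowered because of it, or that gestational age at randomisation is known from the article to be a strong predictor.

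**What to change.** - **Primary estimate:** a Mantel-Haenszel or standardised (marginal) risk difference stratified by gestational age at randomisation (<28/>=28 weeks), with its stratified confidence interval set against the 4-point margin. Both stay on the risk-difference scale of the margin; an adjusted odds ratio would not.
- **Centre:** add it only where cell sizes allow, under a pooling rule fixed in advance.
- **Sequential boundaries:** use the same estimator and its information at each interim and at the end.
- **Sensitivity analysis:** keep the crude difference.
- **Secondary comparisons:** adjust for the same gestational-age stratum.
- **Growth measures:** gestational-age- and sex-specific z-scores may be added as a supportive analysis beside the raw values, not in place of them.

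The cost is revised analysis wording, code, a pooling rule and boundaries matched to the new estimator. No new data or extra recruitment are needed. The change must be prespecified before anyone sees unblinded data. Under the Ethics section it also needs approval from the steering committee, the sponsor, the French medicines agency and the DSMB.
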